**Statement of Compliance**

The trial will be conducted in accordance with the National Statement on Ethical Conduct in Human Research (2007), the CPMP/ICH Note for Guidance on Good Clinical Practice and consistent with the principles that have their origin in the Declaration of Helsinki.

Compliance with these standards provides assurance that the rights, safety and well-being of trial participants are respected. This protocol was developed in accordance with the SPIRIT (Standard Protocol Items: Recommendations for Interventional Trials) 2013 Statement.

**Summary of Approvals and Modifications** (see Summary of Changes from Version 1.0)

Original Approved Version 1.0: 20^th^ January 2020

Modification Approval Version 1.1: 14^th^ March 2020

Modification Approval Version 1.2: 20^th^ April 2020

# Study Objectives and Hypotheses

## 1.1. Primary Aim

To assess the efficacy of the LifeBuoy app in reducing suicidal ideation in young people, as measured by the Suicidal Ideation Attributes Scale. Changes in suicidal ideation will be assessed by comparing the intervention and attention-matched (placebo) control conditions at baseline and post-intervention, and 3-month post intervention follow-up.

## 1.2. Secondary Aim

To assess whether the LifeBuoy app significantly reduces depression, anxiety, and psychological distress, and increases general mental wellbeing at post-intervention and 3-month follow-up, relative to the attention-matched (placebo) control condition.

## 1.3. Tertiary Aims

To examine the engagement with the smartphone application in each condition, assessed as uptake (no. downloads), adherence (no. modules completed) and acceptability among intervention condition participants.

To examine whether there is a dose-response relationship between engagement with the application and the primary outcome (suicidal ideation).

To assess whether the LifeBuoy app significantly reduces insomnia, rumination, suicide cognitions, distress tolerance, and help-seeking intentions and behaviours at post-intervention and three-month follow-up relative to control condition.

To examine whether loneliness, demographics, perseverance, negative events (i.e., such as COVID-19), and expectation of treatment success mediate the relationship between allocated condition and the primary outcome (suicidal ideation).

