**Expectation of Treatment Success**

Four items were created to measure participants’ confidence and readiness in using an app to reduce suicidal thoughts, as well as the perceived importance of reducing suicidal thoughts and participating in research to reduce suicide risk. Items on this scale include ‘I am confident that people could reduce their suicidal thoughts using an app’ and ‘I think that participating in a study that aims to reduce suicidal thoughts is an important thing to do’. These items are rated on a five-point scale (ranging from ‘Strongly disagree (1)’ to ‘Strongly agree (5)’). Other items include ‘Please rate the importance of reducing your suicidal thoughts over the next six months’ (ratings range from ‘Not important (0)’ to ‘Very important (5)’) and ‘Please rate your readiness to reduce your suicidal thoughts by using an app’ (ratings range from ‘Not ready (1)’ to ‘Completely ready (5)’). Due to the nature of these questions, this measure is administered only once during baseline assessment. Total scores indicate higher expectation of treatment success.

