**Table. Overview of Survey Schedule**

| Measure | **Outcome** | **Screening** | **Pre** | **Post** | **4-month** |
| --- | --- | --- | --- | --- | --- |
| Demographics | Demographics | - | X | - | - |
| SIDAS | Suicidal ideation | - | X | X | X |
| PHQ-9 | Depression, suicide attempt | - | X | X | X |
| GAD-7 | Anxiety | - | X | X | X |
| DQ-5 | Psychological Distress | - | X | X | X |
| SGS | Suicide Cognitions | - | X | X | X |
| RTQ-10 | Rumination | - | X | X | X |
| ISI | Insomnia | - | X | X | X |
| SWEMWBS | General mental wellbeing | - | X | X | X |
| DTS | Distress tolerance | - | X | X | X |
| TILS | Loneliness | - | X | X | X |
| GHSQ | Help-seeking intention | - | X | X | X |
| Modified-CSRI | Actual help- seeking | - | X | - | X |
| Modified-NLESS | Negative life events | - | X | - | - |
| SGS | Grit | - | X |  |  |
| Expectations of Success | Expectations of Success | - | X | - | - |
| Satisfaction with app | Satisfaction | - | - | X | - |

Participants in both conditions will be reimbursed for undertaking the post-intervention(T1) and 4-month post-intervention (T2) follow up surveys to reduce attrition at these timepoints. Participants will receive a $20 e-giftcards (from GiftPay; see <https://www.giftpay.com.au/business/egifts.aspx>.) at each of these two timepoints, providing a total reimbursement of $40 per participant if they undertake both surveys.

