# Statistical Analysis

Mixed models repeated measures analyses, with maximum likelihood estimation and an appropriate covariance structure, will be used to evaluate the efficacy of the Lifebuoy app relative to the control condition. The primary outcome is severity of suicidal ideation as assessed by the Suicidal Ideation Attributes Scale [SIDAS] over time (pre- test to post-test; pre-test to follow-up). The mixed models approach incorporates all available data, including participants with missing follow-up data points, under the missing- at-random assumption. Analyses will therefore accord with the intention-to-treat principle. This same approach will be used to examine reductions in secondary outcomes (depression (PHQ-9) anxiety (GAD-7) psychological distress (DQ-5) and wellbeing (SWEMWBS)) and tertiary outcomes (rumination (RTQ-10) insomnia (ISI) general mental wellbeing (SWEMWBS) help-seeking (GHSQ, CSRI)) over time.

Potential mechanisms of the symptom reduction will be measured by the changes in the levels of distress tolerance (DTS), loneliness (TILS) or suicide cognition (SGS). Negative life events (NLESS), grit (SGS) and questions about expectation of treatment success are included in the surveys as potential moderators. Participants’ current medications/interventions will be controlled for data analysis.

Descriptive statistics will be used to evaluate app engagement for participants in both conditions. Adherence will be indicated by the number of modules completed by participants. Participant module access and module completion will be automatically collected via the app. The mixed model approach will be used to determine whether adherence moderates the change in SIDAS scores over time in the intervention condition.

Acceptability of the LifeBuoy app will be examined through semi-structured interviews with a subset of participants and questionnaires in the survey. The interview data will be analysed using thematic analysis [40]. An inductive approach, independent of a theoretical confirmative method will be used to identify and group themes. The researchers will then refine the themes and determine the final coding framework. Discrepancies will be resolved by a third researcher to ensure reliability of the process.

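### Tertiary Aim 1.3 casts measures taken only before randomisation as mediators of allocation, which they cannot be, and contradicts Section 7, which calls three of them moderators

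*Protocol*

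**What the plan says.** **The aim.** The last tertiary aim in Section 1.3 starts from four groups of variables (loneliness, demographics, perseverance and negative events) and asks whether these and "expectation of treatment success mediate the relationship between allocated condition and the primary outcome". Five groups are thus put forward as mediators of the effect on SIDAS.

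**The analysis.** Section 7 divides the variables differently. On mechanisms: "Potential mechanisms of the symptom reduction will be measured by the changes in the levels of distress tolerance (DTS), loneliness (TILS) or suicide cognition". Negative life events are then grouped with two other measures: "grit (SGS) and questions about expectation of treatment success are included in the surveys as potential moderators". Demographics get neither role there.

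**The timing.** The schedule table in Section 6.5 marks demographics ("Demographics | Demographics | - | X"), NLESS, grit and expectation at the pre-intervention survey only. Section 6.4 says of expectation that "this measure is administered only once during baseline assessment". Loneliness, distress tolerance, suicide cognitions and SIDAS are marked at pre, post and follow-up. Section 4.4 places randomisation after completion of the baseline survey.

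**The concern.** A mediator lies on the path from treatment to outcome, so treatment must be able to change it. A value recorded before allocation cannot be changed by allocation. For most of its list, the aim therefore poses a question whose answer is fixed at zero by the design.

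The aim and the analysis section also lead to different models. Someone following Section 1.3 would estimate indirect effects through grit, NLESS and expectation. Someone following Section 7 would fit interactions of those measures with condition. Both could claim to follow the protocol, which leaves room to choose after the data are seen. Two of the three measures that Section 7 treats as mechanisms, distress tolerance and suicide cognition, are missing from the mediation aim; Section 1.3 lists them only as outcomes.

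**Working it through.** **1. Roles and timing side by side.**

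| Variable | Role in Section 1.3 mediation aim | Role in Section 7 | Visits in schedule | Can allocation change it as measured? |
|---|---|---|---|---|
| Demographics | mediator | none given | baseline | no |
| Perseverance (grit) | mediator | moderator | baseline | no |
| Negative events (NLESS) | mediator | moderator | baseline | no |
| Expectation | mediator | moderator | baseline | no |
| Loneliness | mediator | mechanism | baseline, T1, T2 | yes |
| Distress tolerance | not listed | mechanism | baseline, T1, T2 | yes |
| Suicide cognition | not listed | mechanism | baseline, T1, T2 | yes |

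Four of the five groups named in the aim fail the timing condition, and three of those four carry a conflicting role in Section 7.

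**2. The indirect effect of a baseline variable.** Write it as a × b, where a is the effect of allocation on the variable and b its association with SIDAS given allocation. Randomisation after measurement makes a = 0, so a × b = 0 whatever b is.

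The protocol gives no b, so take b = 0.5 in standard deviation units as an assumption, with N = 378 in equal arms:

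- SE of the estimated a = 2/√378 = 0.103, so the estimated a × b has a standard deviation of about 0.5 × 0.103 = 0.051.
- SE of b ≈ √(1 − 0.25)/√378 = 0.045, so b is almost always significant. A joint-significance test then declares mediation about as often as the test of a rejects, near 5%.
- Simulation (4,000 trials): mean indirect effect −0.0005, standard deviation 0.052, mediation declared in 5.2%. With N = 264 the rate is 5.1%.

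Each such finding reflects chance baseline imbalance.

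**3. The plan's own figure.** Section 8 gives d = 0.30, pre-post correlation 0.50, attrition 30%, power 0.80 and alpha 0.05 (two-sided assumed). With baseline adjustment, n = 2 × (1.96 + 0.84)² × (1 − 0.50²)/0.30² ≈ 131 per arm. The noncentral t version gives 132, and 132/0.7 = 188.6, so 189 per arm. The stated 378 is reproduced, and nothing in this point changes it.

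**4. What existing visits allow for the real candidates.** T1 precedes T2, whether follow-up is taken as 3 or 4 months, so a T1 mediator can be related to T2 SIDAS. If 30% attrition also holds at T2, about 0.7 × 378 ≈ 264 people remain. The protocol gives no a or b here, so a range is shown (joint significance, 2,000 simulated trials per cell, adjusted for allocation only, no direct effect):

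| a (SD units) | Power, b from 0.2 to 0.5 |
|---|---|
| 0.2 | 0.33 to 0.37 |
| 0.3 | 0.61 to 0.69 |
| 0.4 | 0.81 to 0.90 |
| 0.5 | 0.89 to 0.98 |

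As a check, at a = 0.2 the SE of a is 2/√264 = 0.123, and the normal approximation gives power Φ(0.2/0.123 − 1.96) ≈ 0.37 for the a path alone.

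**5. One label, two scales.** Both the schedule and Section 7 use SGS for suicide cognitions and for grit. Section 6.3 and Appendix C abbreviate the former SCS. One abbreviation therefore names both a mechanism and a moderator.

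**The case against.** The strongest reply is that Section 7 is the operative text and already assigns most roles correctly, so the fault is one wrong word in a tertiary aim. The writers may simply have meant *moderate*. The impossible analyses would be run only if the aim overrode Section 7, and the false-positive rate would then be near nominal. Much of this stands and limits the weight of the point. It does not remove it: the aim asks for a different analysis from the one in Section 7, and demographics are not rescued by Section 7 at all.

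Four stronger readings are tempting and not supported:

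- **That everything under negative events is baseline-only.** The aim mentions COVID-19, and the Summary of Changes (Version 1.2) adds ten COVID-19 items without stating their visit. Baseline-only timing is shown for NLESS, not for those items.
- **That loneliness is equally impossible.** It is measured at all three visits and can be a mediator.
- **That the plan overlooks the plausible mechanisms or ties them to same-visit changes.** Section 7 names them and says only that changes in level will be used. It fixes no visit, and the detail of a mediation model may properly sit in the SAP, which is not at hand.
- **That a lagged model should adjust for T1 SIDAS.** This would remove any indirect effect already expressed by T1, the visit at which H1 expects the benefit.

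**Conclusion.** The point holds as a contradiction, and as an aim that the schedule makes impossible for demographics, grit, NLESS and expectation: four of five named groups, subject to the reservation about the COVID-19 items. The zero indirect effect follows from the order of measurement and randomisation and needs no numerical assumption. The 5% rate and the power figures depend on the assumed paths and, for the latter, on 30% attrition at T2. The consequence is confined to a tertiary aim. H1 to H3, the primary analysis and the sample size are untouched. It is worth correcting because the wording decides which analysis answers a stated aim and the correction is nearly free.

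**What to change.** - In Section 1.3, replace *mediate* with *moderate* for grit, negative life events (NLESS) and expectation.
- Treat demographics as baseline moderators or predictors, and say which ones; Section 6.4 lists many, and leaving them open invites an unlimited set of interaction tests.
- Name loneliness, distress tolerance and suicide cognition as the candidate mediators, as in Section 7.
- In the schedule and Section 7, use SCS for suicide cognitions and keep SGS for grit.

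The cost is the wording of one aim and a label.

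Optionally, add an exploratory analysis relating each T1 mediator to T2 SIDAS, adjusted for the baseline mediator and baseline SIDAS, but not for T1 SIDAS if the total indirect effect is wanted. It needs no new visit. Its costs are reliance on those present at T2, limited power for small effects of allocation on the mediator, and a mediator-outcome path that is not randomised and so stays open to confounding. It would not explain the post-test effect in H1: mediator and outcome are both measured at T1 there, and the 3-week safety check collects only the SIDAS screener.

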## 1.4. Hypotheses

H1: Participants in the intervention condition will report greater reductions in suicidal ideation scores at post-intervention compared to the placebo control condition.

H2: Participants in the intervention condition will report greater reductions in depression and anxiety symptoms at post-intervention than the control condition.

H3: Higher levels of adherence to the LifeBuoy app will be associated with greater reductions in suicidal ideation at post-intervention.

# Study Background

## 2.1. Rationale

Youth suicidal ideation and behaviour remain a major public health concern because of their life-threatening nature and widespread prevalence. It is an issue that exists across psychiatric diagnoses and in varied socio-cultural populations. In Australia, suicide is the leading cause of death among those aged 15 to 44 years [1]. The importance of the problem of suicidality is further highlighted by its prevalence in the general population. Suicidal ideation is relatively common among adolescents, with 12-month prevalence estimates as high as 24% in those aged 18 or younger [2]. Over one‐third of adolescents who experience suicidal ideation go on to attempt suicide [3]. Youth suicide also carries significant economic loss, which is estimated to be $511M per annum [4].

The extent of suicidality is, at least in part, compounded by adolescents’ reluctance to seek help for psychological distress and suicidality. A recent review [5] reported that of 12,006 individuals with past-year suicide ideation, plans, and/or attempts, the weighted average prevalence of seeking or engaging with mental health services was 29.5%. Lower rates of help- seeking were associated with being younger, being male, and cultural influences [5,6]. Potentially up to 70% of young people have not sought or received access to mental health services. Traditional face-to-face treatment services also have numerous economic, logistical, and personal barriers (i.e., stigma) that prevent most young Australians from accessing them [7]. Digitally delivered interventions offer a new opportunity to detect at risk young people, improve access to support, and provide high fidelity/cost-effective treatment, addressing gaps observed in current population and health system approaches.

There is emerging evidence that adults readily access, and benefit from, suicide prevention interventions delivered via smartphone-based apps [8]. However, there have been very few empirical studies examining the efficacy of mental health apps for young people, and there are even fewer studies for apps that specifically target suicidal thoughts in this population. Of those interventions which have undergone RCT testing, only two have been mHealth (mobile phone, tablet) programs (and none specifically for young people), despite estimates that 94% of young people own a smartphone and that they spend up to one-third of their day using electronic devices (phones, computers) [9]. Considering these levels of smartphone ownership and use it is surprising that they remain relatively unexplored as a digital health solution in suicide prevention. To address this gap, we developed the LifeBuoy app, a self-help smartphone app designed to help young adults manage suicidal thoughts and negative feelings in daily life. It includes seven structured therapeutic sessions derived primarily from Dialectical behaviour therapy (DBT), which has been shown to reduce suicide-related outcomes, including non-suicidal self-injurious behaviour (NSSI) and suicide attempts [10,11]. DBT combines principles from behaviorism, Zen, and dialectics [12] that aim to help clients improve their emotional and cognitive regulation to overcome problems, including intense mood change [13,14], impulsivity [15,16], and loneliness [17]. DBT was initially developed for persons diagnosed with borderline personality disorder [18], and there is increasing evidence to suggest that DBT is also effective in reducing suicidal thoughts, NSSI, and suicide attempts in both adults [19] and adolescents [20,21]. To our best knowledge, no studies have investigated the possibility of a using a DBT-informed app to reduce suicidal thoughts in young adults.

We also recognise that the use of mental health digital interventions is highly variable between 21% - 88% engaging in minimal use, and 7% – 42% engaging in moderate use [22]. To overcome challenges with engagement, young people with a lived experience of suicide were surveyed and interviewed to identify features, content, and aesthetics that appealed to the target age group (e.g. available offline, well-organised and logically-linked content, youthful language, bright colours, and, positive illustrations, pace personalisation, self-monitoring and progress feedback) as factors that would improve engagement and adherence. These principles have been embedded in the LifeBuoy app, to minimise the risk of trialling an app that will not be used, or which is used very minimally.

## 2.2. The LifeBuoy Study.

The LifeBuoy study aims to evaluate whether a therapeutic smartphone application is effective and acceptable for reducing suicidal ideation l in young adults, aged 16 to 25 years who have experienced suicidal ideation in the past 12 months and. It tests an interventional smartphone application (LifeBuoy) against a matched attention control application (LifeBuoy-C) so that individuals will not know which app they have downloaded. The findings of the current study are important in providing initial evidence of whether smartphone applications are able to deliver accessible health interventions to young people.

# Study Design

## 3.1. Treatment Design

The flowchart (Figure 1) summarizes this study which will consist of evaluating the efficacy of a digital therapeutic for suicidal ideation, using a is a two-arm, parallel, double-blind superiority randomised controlled trial design. Following completion of the baseline (T0) assessment, participants will be randomised at equal allocation (2:2) to one of two smartphone applications, a DBT-based application (LifeBuoy) or a placebo (non-therapeutic) control application (LifeBuoy-C). After completion of the 6 week intervention, primary, secondary and tertiary outcomes will be assessed at immediate post-intervention (T1) and then at 4-months post-intervention (T2). All surveys will be completed online, with survey links distributed automatically to registered participants using Black Dog Institute’s research engine. Subjects in the intervention condition will be invited to participate in a qualitative intervention at the final assessment to understand their experience with the LifeBuoy application.

[figure not shown]

**Figure 1. Study flow**

## 3.2. Randomisation

Randomisation to the active or control condition will occur on a 2:2 ratio using a block design (4 participants per block) using an automated web-based platform tailored for this project. Randomisation codes will be generated and retained automatically by the Black Dog Institute’s bespoke trial software, the research engine.

## 3.3. Study Population

Our sample will consist of 378 community-based young adults aged between 16 and 25 years who have experienced suicidal ideation in the past year, recruited using an online, social media strategy. The overall goal of the inclusion/exclusion criteria is to identify a non-clinical population of suicidal ideators.

# Selection and Enrollment of Subjects

## 4.1. Inclusion and Exclusion Criteria

The inclusion criteria are as follows and will be determined by an online self-reported screening survey.

Participants will be deemed **eligible** if they:

- Are 16 to 25 years old (inclusive)
- Are living in Australia
- Are fluent in English
- Own and have access to a smartphone
- Experienced mild to moderate suicidal thoughts in the past year (SIDAS scores < 21).

Participants will be **ineligible** if they:

- Have ever been diagnosed with psychosis or bipolar disorder
- Have made a suicide attempt in past month.

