# Appendix A: Recruitment materials

**The LifeBuoy App: A randomised controlled trial of a mHealth intervention to help young people manage suicidal thoughts**

We are looking for young people who have experienced suicidal thoughts to participate in a study evaluating the effectiveness of a smartphone app “LifeBuoy” that is designed to reduce suicidal thoughts.

We need young people who:

- Are 16-25 years old;
- Are living in Australia;
- Are fluent in English;
- Own and have access to a smartphone;
- Have experienced suicidal thoughts in the past year;
- Have not been diagnosed with psychosis or a bipolar disorder;
- Have no suicidal attempt or plan in the past month.

Eligible participants will:

1. Be assigned to one of two groups: an intervention group (who receives the therapeutic app) or a control group (who receives a non-therapeutic app). All participants will then follow the same process;
2. Complete 7 modules in the app over 6 weeks (total 1 hour);
3. Complete an online survey on 3 occasions: before (35 minutes) and after completing all modules (25 minutes), and then 3 months after the completion of all modules (25 minutes). The survey will include questions about your demographics, suicidal thoughts and suicide attempts, negative life events, how you have been feeling lately, sleep, help-seeking intentions and experience, perseverance, and expectations of and satisfaction with the app;
4. Download an app called ‘Lifebuoy’ after completing the first survey, (you will not know whether you are receiving the intervention or control version of this app). Both apps will be available for 6 weeks for use on your personal smartphone. If you receive the control app, you will be informed after the final survey to let you know that you were in the control condition, and what that means.
5. Receive a $20 gift card in acknowledgement of your time and internet expenses related to participation in each follow-up survey (total $40 gift card if you complete both follow-up surveys).

Please note: suicide related questions will be asked in the online survey. Participants are free to withdraw at any time. The identified information obtained in this study will remain confidential and be stored in an archive on the UNSW server hard drive for a period of 7 years.

If you are interested in participating this study, please click here <Insert link: XXX>.

This study has been approved by Human Review Ethics Committee at the University of New South Wales [HC190764]

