**Advertisement for social media channels**

The Black Dog Institute is inviting young people aged 18-25 who have experienced suicidal thoughts to participate in a study evaluating the effectiveness of a smartphone app designed to reduce suicidal thoughts. You will receive $40 in appreciation for your time in participating. This study involves the completion of 7 app modules over 6 weeks (1 hour total), and one online survey before starting the app (35 minutes) and two surveys after (immediately and 3-months later; 25 minutes each).

Click here <Insert the link to the recruitment page> to get more information. Lifeline: [name].

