**Short version of the advertisement**

The Black Dog Institute is inviting young people aged between 16-25 who have experienced suicidal thoughts to evaluate the effectiveness of a smartphone app designed to reduce suicidal thoughts. You will receive $40 in giftcards for participating.

Click here<Insert the link to the recruitment page> to know more. Lifeline: 13 11

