# Appendix B: Screening and Eligibility

**Screening questions**

| **What the participant will see** | | **Drop down response options available** |
| --- | --- | --- |
| Are you aged between 16 and 25? | --- select --- | Yes, I’m between 16 and 20 years old  Yes, I’m between 21 and 25 years old  No |
| Are you living in Australia currently? | --- select --- | Yes  No |
| Are you fluent in English? | --- select --- | Yes  No |
| Do you own, or have access to, a smartphone (iOS or Android)? | -- select --- | Yes  No |
| Have you experienced suicidal thoughts in the past 12 months? | -- select --- | Yes  No |
| Have you attempted suicide in the past month? | -- select --- | Yes  No |
| Have you ever been diagnosed with psychosis or bipolar disorder? | -- select --- | Yes  No |
| Gender assigned at birth | -- select --- | Male  Female |

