**Study Summary**

Involving young people aged 18 – 25 years from the Australian general community, this randomised controlled trial (RCT) will examine the use of a smartphone application (‘LifeBuoy’) to deliver digital Dialectical Behaviour Therapy (DBT) and Acceptance and Commitment Therapy (ACT) to reduce symptom severity of suicidal ideation. This study will rely on self-report data to evaluate the efficacy of the app. This study is funded by the Roth Family Foundation and an Australian Rotary Health Youth Mental Health Grant for 2 years.

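### The current protocol text states two minimum ages, 16 and 18, and the automated screening route would admit 16- and 17-year-olds to a trial the DSMB charter describes as 18–25

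*Protocol*

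**What the plan says.** Most of the protocol uses a minimum age of 16. The study overview in section 2.2 describes participants "aged 16 to 25 years who have experienced suicidal ideation in the past 12 months". Section 3.3 plans for "378 community-based young adults aged between 16 and 25 years". The inclusion criterion in section 4.1 is "Are 16 to 25 years old (inclusive". In Appendix A, the main recruitment text asks for people who "Are 16-25 years old", and the short advert is "inviting young people aged between 16-25 who have experienced suicidal thoughts". The screener in Appendix B asks whether the person is between 16 and 25, and its lower answer is "Yes, I’m between 16 and 20 years old". The baseline age list in Appendix C starts at 16.

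Two places use 18. The social-media advert in Appendix A reads "The Black Dog Institute is inviting young people aged 18-25 who have experienced suicidal thoughts". The Study Summary in the DSMB charter (Appendix E) reads "Involving young people aged 18 – 25 years from the Australian general community".

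**The concern.** Minimum age is a core eligibility limit, and here it decides whether minors enter a trial of suicidal young people. The protocol's recruitment wording, eligibility instrument and safety charter should describe one population, and they do not.

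Three things depend on the answer. The first is who is invited: one advert addresses 18–25 and the other 16–25, although section 4.2 says the adverts are targeted to the inclusion criteria. The second is oversight: the charter is approved by the board's members, and the population it describes is narrower than the one the screener lets in. The third is reporting: the age range to which the result applies is stated in two ways.

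**Working it through.** The sources do not call for a formula. The check sets the age statements side by side and follows the written route to randomisation.

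**Step 1: the statements.**

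| Place in the protocol | Minimum age |
| --- | --- |
| Section 2.2, overview | 16 |
| Section 3.3, study population | 16 |
| Section 4.1, inclusion criterion | 16 |
| Appendix A, main recruitment text | 16 |
| Appendix A, short advert | 16 |
| Appendix B, screener | 16 |
| Appendix C, baseline age list | 16 |
| Appendix A, social-media advert | 18 |
| Appendix E, DSMB charter, Study Summary | 18 |

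Seven places give 16 and two give 18. All nine are current text, so the conflict does not depend on the Summary of Changes.

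**Step 2: the route to randomisation.** Section 4.1 says eligibility is determined by an online self-report survey. Section 4.3 sends eligible people on to registration automatically. Section 4.4 randomises them by algorithm once the baseline survey is complete. No age check by staff is described. A 17-year-old who answers the Appendix B question truthfully therefore passes, registers, completes baseline and can be randomised.

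**Step 3: each possible limit in turn.**

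- If the approved limit is 16, the screener implements the criterion correctly. The social-media advert then fails to invite eligible 16- and 17-year-olds, and the charter describes the wrong population.
- If the approved limit is 18, sections 2.2, 3.3 and 4.1, two of the three recruitment texts, the screener and the baseline list are wrong. The lower screener answer covers ages 16, 17, 18, 19 and 20: two ineligible ages and three eligible ones under a single response. Appendix C does collect single-year age before randomisation, but its list admits 16 and 17 and no described step uses it to stop anyone. Each person under 18 who was enrolled would match an example of a protocol deviation in section 11.1, the inclusion of someone who does not meet the criteria. Section 4.5 keeps data collected after baseline.

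**Step 4: size.** The list from 16 to 25 has 25 − 16 + 1 = 10 single-year ages, of which two (16 and 17) are in dispute. This counts ages, not people.

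**Step 5: the powered figure.** Section 8 gives d = 0.30, a pre–post correlation of 0.50, 30% attrition, power 0.80 and alpha 0.05 (taken here as two-sided). With baseline adjustment, n per arm = 2 × (1 − 0.50²) × (1.960 + 0.842)² / 0.30² ≈ 131. Allowing for attrition, 131 / 0.70 gives 188, against the stated 189. Age does not enter this calculation, so the conflict leaves the planned sample size as it stands.

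**The case against.** The strongest reply is that the protocol has only one eligibility rule, in section 4.1, and it says 16. An advert and a descriptive summary in an appended charter do not set eligibility. The range 18–25 lies wholly inside 16–25, so nobody invited by the narrower advert fails section 4.1 on age. The only entry that gives 18 as the minimum for inclusion is in the Summary of Changes, and a difference between a change log and the text is not in itself an error. Section 4.3 lists age among the screening questions and Appendix C records exact age before allocation, so the information needed to apply either limit is collected before allocation.

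Much of this stands. Against section 4.1 as written, the screener works, and a 17-year-old who passes is eligible. The claims about deviations and about the screener failing hold only if 18 is the approved limit. Keeping randomised participants in the analysis is ordinary intention-to-treat practice and no added fault.

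The reply does not remove the mismatch. With the Summary of Changes set aside, the social-media advert and the charter still disagree with section 4.1, and the two adverts still disagree with each other.

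A reader might also infer that minors are in fact being randomised, or that the trial has no defined age range. The documents support neither. The first goes beyond a written procedure that permits it. The second overlooks sections 2.2, 3.3 and 4.1, which agree with one another; the range is stated inconsistently, not left open.

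**Conclusion.** The point holds as an internal contradiction on a core eligibility limit, and it should be resolved whichever age is right. The documents reviewed do not settle which limit is approved, and this review does not choose one.

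The conclusion that 16- and 17-year-olds can be randomised rests on the procedure described in sections 4.1, 4.3 and 4.4 and Appendix B, and assumes no undescribed age check in the trial software.

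It is tempting to attach a head-count: even enrolment across the ten ages would give 0.20 × 378 ≈ 76 participants, and assumed shares of 10% or 30% would give about 38 or 113. The documents give no age distribution and one advert addresses only 18–25, so these figures show only how far the answer moves with the assumption. The number affected cannot be derived. The importance of the point comes from the possible entry of minors and the mismatch with the safety board's charter.

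**What to change.** Confirm the one approved age range and state it identically in sections 2.2, 3.3 and 4.1, all three recruitment texts in Appendix A, the screener in Appendix B, the age list in Appendix C and the Study Summary of the DSMB charter. Have the board's members confirm the corrected charter.

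Replace the two age bands in the screener with single-year age, using the question that already exists in Appendix C, and have the research engine stop anyone outside the range before registration. This is essential if the limit is 18. If it is 16, the present bands already match the criterion and the change is a safeguard.

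The cost is wording edits, one changed drop-down and one automatic rule. If 18–25 is confirmed, the recruitment pool is somewhat smaller than the current criterion allows.
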